**Activities**
***Walking***
Walking with visual cues or attention strategies to correct step size to criterion length. Incorporate stopping and starting, with auditory cues if gait initiation difficulties.
***Turning***
Walking while turning, in either 'arc' or 'clock' (on the spot) patterns. Cues may include tape on floor, cue cards, photos, with attention to step size and placement.
Practise different turn magnitudes and turn activities relevant to home and community environment.
***Reaching in Standing***
Practice varied reaching activities in functional contexts, progressing to reach for objects of different weights and sizes at differing heights. Emphasise conscious attention to postural stability and position prior to reach.
***Sit to stand***
Modify chair height to assist or challenge patient, practise from different styles of chairs, chair height and compliances of chair and floor surface. Emphasise conscious attention to movement sequence in conjunction with amplitude, speed and flow of movement. Use visual cues such as photos or cue cards with key words.
***Transfer from chair to chair***
Practice transferring from chair to chair with the seats in different configurations, including at tables and in theatre rows. Encourage conscious attention to movement components in sequence and ensure safety. Visual and auditory cues may include cue cards with key words or pictures.
***Getting up from bed***
Emphasise normal timing and maintain momentum. Practise from same side of bed as person uses at home. Use assistive devices such as a bedpole where appropriate. Attentional strategies should focus on position in bed, sequence and speed and flow of movement. Cues could include cards with key words, photos or pictures.
***Protective stepping in standing***
Practise taking quick, large steps in different directions. Practise responding quickly to a verbal cue to step, or to a tug or push in a known or unknown direction. Encourage attentional strategies, such as focussing on visualising big and fast steps in the direction of loss of balance.
***Complex walking tasks***
Practice dual or multi-tasks, and obstacle course negotiation. Encourage mental preparation or movement visualisation, with pre-planning of the obstacle course and recognition of potentially difficult areas.

#### Progressive resistance strength training

The PST intervention group will attend a physical therapy program of equivalent length to the MST group; two hours weekly for eight weeks in an outpatient setting, in small classes of three or four participants. The PST program will include strengthening exercises for quadriceps, hip and trunk extensor muscles, hip abductors, calf, and ankle dorsiflexors, tailored to the individual's strength and functional ability. Table 2 summarises the content and dosage of PST with guidelines for therapists. Where possible, training is performed in functional tasks such as standing up from a chair, stepping up onto a step etc, using body weight, weighted vests and Thera-band^® ^to progress the resistance. Structured falls risk education will also be provided each week, in a manner identical to the MST group, using the same *Don't fall for it. Falls can be prevented! - A guide to preventing falls for older people *resource booklet [28]. An individualised home practice session of strengthening exercises will also be completed once per week. A single home visit will be conducted by a trained therapist or nurse to check compliance with the therapy program.

**Table 2 T2:** Progressive Resistance strength training protocol

**2. Principles of Progressive Resistance Strength Training **[17,18,20,21,45]

• Safety is paramount. Ensure
○ correct execution of the movement
○ the required number of repetitions and sets is achieved
○ the required level of supervision or support is provided
○ participants advise therapists of any concerns or adverse symptoms
• All exercises will be steadily progressed, either by
○ increasing the number of repetitions (aim for 8-15)
○ increasing the weight or resistance (2% bodyweight increments)
○ altering starting position
○ increasing number of sets (to maximum of 3)
• Progression is guided by
○ the participant's ability to correctly perform the movement
○ the Modified Perceived Exertion scale (mRPE) [45] - when the exercise level is ≤ 5 on this scale
○ completion of 8-15 repetitions for 1-2 sets
○ clinical judgement of the therapist

**Exercises**
***Sit-to-stand***
Sit to stand from chair. Progress with variation of use of arms, vary height of chair and use of weighted vest.
***Trunk extension and rotation***
Seated, Thera-band^® ^loop under one foot, use both hands, (i) flex elbows until hands touch opposite shoulder, then (ii) rotate and extend trunk.
***Lateral pelvic hold/hitch***
Subject single leg stance on small step and hand support. Shorten or hitch so pelvis is horizontal and hold for count of 5 - 30 secs. Progression includes use of weighted vest.
***Step-ups***
Subjects stand in front of step with hand support nearby. Step up then return, first with right leading, then with left leading. Progression includes use of weighted vest.
***Heel raises***
Participants stand facing wall, toes approximately 40 mm from wall. Lean forearms on the wall, then push up onto the balls of the feet. Hold for count of 10. Progression includes use of weighted vest.
***Standing toe raises keeping balance***
Standing upright, with back close to wall for safety, raise one forefoot, hold, then down, followed by the other.
Progress to both feet together, then standing toes down on a wedge.
***Abdominals***
Subject sitting on edge of a chair with a back, with hands on opposite shoulders. Keeping back straight, and abdominals braced, lean backwards a short distance. Hold for count of 5 - 10.

#### Life-skills control group

The control intervention will be of equivalent duration to the MST and PST groups, delivered in small groups in outpatient settings over 8 weekly two hour sessions. Each session will be led by trained occupational therapists, physical therapists, speech pathologists or social workers, and include content such as relaxation, games, or communication activities. Guided discussion will also include topics such as the impact of PD on the individual and family, support and resources available, and fatigue management. None of the content will relate to walking, balance or falls risk education. A home session of reflection activities and relaxation practice will also be completed once per week.

### Outcome measures

All participants will be tested by trained blinded assessors before and after the 8 week interventions, and at 3 months and 12 months after completion of the intervention phase. Participants will keep a falls calendar for 12 months after therapy. Consistent with the recommendations of the Prevention of Falls Network Europe (PrOFaNE) group, a fall will be defined as "an unexpected event in which the participant comes to rest on the ground, floor, or lower level" [35]. Each time a participant falls, they will tick the date on the falls calendar and then telephone a falls hotline where they will be interviewed about the nature of the fall, circumstances, injuries sustained, healthcare required and other factors. The falls interview questions are given in Figure 1, and an example of a calendar page is provided as an additional file (see Additional File 1).

**Figure 1 F1:**
[figure not shown]
**Falls interview questions**.

The three falls outcomes that are the primary outcomes are (i) the number of fallers in each group (ii) the number of multiple fallers in each group and (iii) the falls rate over 12 months in each group. Secondary outcome measures will include the number of injurious falls, defined as a fall requiring a visit to a health service provider. Additional secondary outcome measures include mobility, measured by quantifying walking speed using the 6m walking test and the Timed Up and Go Test [36]. Activity limitations will be quantified using the United Parkinson's Disease Rating Scale sections II and III [37]. Quality of life will be measured using the Parkinson's Disease Questionnaire-39 (PDQ39) [38] and EuroQol-5D [39]. Changes in health-related QoL will be measured using both a PD-specific measure (PDQ-39) and a generic utility instrument (Euroqol-5D) administered at baseline, immediately post-intervention, 3 months, and 12 months. Safety during the intervention phase will be assessed by time to first fall, and monitoring of adverse events related to therapy.

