## Methods

### Design

A single blind, parallel-group randomised controlled clinical trial (RCT) design will be used with two intervention groups and one control group. Because the literature at the time of study design did not provide evidence on whether movement strategies were superior to strengthening, we included one group receiving MST and another receiving PST. To reflect clinical practice, each of these groups will also receive a falls prevention education program [28]. A control group that does not include physical therapy or falls education will be used to determine the relative effectiveness of each therapy approach. Ethical approval to conduct the study has been gained from the University of Melbourne Health Sciences Human Ethics Sub-Committee (0828579). Written consent for publication will be obtained from the participant or their relative.

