### Statistical analysis

Statistical analysis will be undertaken using IBM SPSS version 19.0 (SPSS Corp, Chicago, Ill, USA) and STATA 8 (Stata Corp, College Station, Tex., USA) statistical software. All analyses will be conducted on an intention-to-treat principle using all randomised participants. Demographic characteristics and baseline data will be summarised by descriptive statistics. For the primary outcome measures, the number of fallers and multiple fallers in each group will be compared by calculating relative risks. The number of falls and falls rate per person per year in the three groups will then be compared using negative binomial regression models. This approach takes into account all falls and adjusts for varying duration of follow-up [40,41]. As a safety measure, time to first fall during the intervention period will be analysed using Kaplan-Meier survival analysis, and comparisons between groups will be made using the Mantel-Cox log rank test. The continuously-scored secondary outcome measures at baseline and the follow-up appointments will be compared using analysis of covariance with baseline scores and intervention group entered as independent variables [42,43]. For categorical secondary outcome measures, relative risks will be used to analyse differences between the groups.

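### Non-fall adverse events are counted only if related to therapy, which tends to remove the control arm's background rate and biases any estimate of excess non-fall harm

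*Protocol article*

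**What the plan says.** The protocol article, under Methods, Outcome measures, names two safety measures for the 8-week phase: "Safety during the intervention phase will be assessed by time to first fall, and monitoring of adverse events related to therapy". The first is unconditional and the second is conditional on cause.

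The Statistical analysis section takes up only the first: "As a safety measure, time to first fall during the intervention period will be analysed using Kaplan-Meier survival analysis". The arms are then compared by a log rank test. It states no analysis of adverse events by group.

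The Design section describes the comparator: "A control group that does not include physical therapy or falls education will be used to determine the relative effectiveness of each therapy approach". The Life-skills control group section lists relaxation, games, communication activities and guided discussion, and adds: "None of the content will relate to walking, balance or falls risk education".

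**The concern.** A randomised control arm shows how often events occur without the treatment. Background events are to be expected in people with Parkinson's disease over eight weeks, whatever program they attend. The excess in an active arm is its event rate minus the control rate, and that holds only if events enter the count by the same rule in each arm.

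A relatedness condition is not the same rule in each arm. A strained muscle after resistance exercise is readily attributed to the program. The same strain in someone attending relaxation and discussion sessions is not. The chance that an event is counted then depends on allocation.

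At stake are the non-fall harms of two physical programs, one of which progresses resistance with weighted vests (Table 2). Falls data do not capture these harms. Events left out at collection cannot be reliably recovered at analysis.

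**Working it through.** The article gives no adverse-event figure to reproduce. The check is a comparison of texts, followed by simple algebra on assumed values.

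**Texts side by side**

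| Safety item | Where stated | Conditional on cause? | Comparison between groups stated? |
|---|---|---|---|
| Time to first fall, intervention phase | Outcome measures; Statistical analysis | No | Yes, log rank test |
| Injurious falls (secondary outcome) | Outcome measures | No, defined by a visit to a health service provider | Not by name |
| Other adverse events, intervention phase | Outcome measures | Yes | No |

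The fall definition, "an unexpected event in which the participant comes to rest on the ground, floor, or lower level", applies to every participant and carries no causal condition. Only the third row has the problem.

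**Effect of the filter**

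Let p_A and p_C be the true proportions with a non-fall event in an active arm and in control. Let c_A and c_C be the probabilities that such an event is judged related and so counted.

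- Recorded proportions: p_A × c_A and p_C × c_C.
- Recorded relative risk: (p_A / p_C) × (c_A / c_C).
- Recorded risk difference: p_A × c_A − p_C × c_C.

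The true ratio is recovered only if c_A = c_C. The true difference is recovered only if, in addition, both equal 1, apart from chance cancellation. The article gives none of the four quantities, so neither contrast can be corrected afterwards.

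**Illustration (all inputs assumed, except 110 per arm from Sample size)**

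Take p_A = p_C = 0.20, so there is no true difference, and c_A = 0.90. The active arm records 0.20 × 0.90 = 0.18, or 110 × 0.18 = 19.8 people.

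| c_C | Control recorded | People per 110 | Apparent relative risk | Apparent difference |
|---|---|---|---|---|
| 0.80 | 0.20 × 0.80 = 0.16 | 17.6 | 0.18/0.16 = 1.13 | 2 points |
| 0.60 | 0.20 × 0.60 = 0.12 | 13.2 | 0.18/0.12 = 1.50 | 6 points |
| 0.40 | 0.20 × 0.40 = 0.08 | 8.8 | 0.18/0.08 = 2.25 | 10 points |

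The apparent relative risk is simply c_A / c_C. The table shows how the mechanism works and does not predict this trial's result.

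The bias need not always exaggerate harm. If c_A = c_C = 0.60, the ratio is right but a true excess is recorded at 60% of its size on the difference scale.

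**The case against.** The case on the other side is substantial, and much of it stands.

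- **Safety as a whole.** A reader might infer that safety cannot be fairly compared between the arms at all. The documents do not support this. Time to first fall has no causal filter and is compared between groups, and injurious falls are also unfiltered.
- **Prompting.** A reader might infer that PST is asked about symptoms and the other arms are not, because only Table 2 has the line "participants advise therapists of any concerns or adverse symptoms". That line stands among instructions for delivering resistance exercise safely, beside correct execution and level of supervision. It is not presented as the trial's way of collecting adverse events. A condensed article may leave that method to the full protocol, so the lack of a matching line for MST or control shows nothing about unequal prompting.
- **Who judges.** A reader might infer that unblinded class therapists decide relatedness. The article does not say who decides.
- **Meaning of therapy.** The word is sometimes used for all arms: the Abstract has every participant receiving therapy, and everyone's falls calendar runs after therapy. Events caused by the life-skills program could therefore qualify. Elsewhere, as in Sample size, active therapy means MST and PST only. The ambiguity removes any claim that the control count must be near zero. It does not remove the filter: even on the broad reading, an event must be attributed to the program, and exercise and discussion do not attract attribution equally.
- **No promised comparison.** The article speaks of monitoring and commits to no between-arm analysis of these events, so the plan does not promise a biased result. But followed as written, the data needed for an unbiased comparison would not exist.
- **Condensation.** What an article leaves out is no finding. Here, however, the scope is stated, and the stated scope is the problem.

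**Conclusion.** The point holds for non-fall adverse events in the 8-week phase and no further. As worded, the scope depends on presumed cause. The control has no physical therapy, so the condition tends to remove control-arm background events, and excess non-fall harm in MST or PST over control cannot be estimated without bias. The primary falls outcomes and the fall-based safety measures are unaffected.

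The size is unknown. The apparent relative risks of 1.13 to 2.25 rest entirely on assumed rates.

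The conclusion assumes that the sentence is followed literally, so that events judged unrelated are not recorded in a comparable form. If the full protocol already collects every event in all arms, only the wording here needs correcting. This is an inexpensive improvement to a secondary safety item and does not threaten the trial's main conclusions.

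**What to change.** Reword the safety sentence in Outcome measures so that all adverse events during the 8-week phase are recorded in the same way in all three arms, regardless of presumed cause. Summarise them by arm. Report relatedness as a separate descriptive item that does not decide whether an event is counted. Time to first fall stays as it is.

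The change must be in place before data collection. It costs a change of wording and a longer list of background events to record and report.

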### Statistical analysis

Statistical analysis will be undertaken using IBM SPSS version 19.0 (SPSS Corp, Chicago, Ill, USA) and STATA 8 (Stata Corp, College Station, Tex., USA) statistical software. All analyses will be conducted on an intention-to-treat principle using all randomised participants. Demographic characteristics and baseline data will be summarised by descriptive statistics. For the primary outcome measures, the number of fallers and multiple fallers in each group will be compared by calculating relative risks. The number of falls and falls rate per person per year in the three groups will then be compared using negative binomial regression models. This approach takes into account all falls and adjusts for varying duration of follow-up [40,41]. As a safety measure, time to first fall during the intervention period will be analysed using Kaplan-Meier survival analysis, and comparisons between groups will be made using the Mantel-Cox log rank test. The continuously-scored secondary outcome measures at baseline and the follow-up appointments will be compared using analysis of covariance with baseline scores and intervention group entered as independent variables [42,43]. For categorical secondary outcome measures, relative risks will be used to analyse differences between the groups.

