### Sample size

The sample size for the study was determined based on the falls rates and effect sizes obtained from previous trials on people with PD and the elderly [6,31,32]. For each sample size calculation, power was set at 80%, alpha set at 5%, and the drop-out rate was set at 15%. For falls, a sample size of 110 was thought to be required to detect a 20% difference between the groups, assuming a falling rate of 60% in the control group. For walking speed, a sample size of 74 was required to detect a 10% difference between the groups, assuming a mean (± SD) walking speed in the control group of 58.4 (12.0) m/min. For the "timed up and go" test, a sample size of 83 was thought to be required to detect a 10% difference between the groups, assuming a mean (± SD) timed up and go in the control group of 13.78 (2.99) sec. Thus, to ensure adequate statistical power for each of these outcome measures, the sample size for the study would optimally be 110 per group (total n = 330). Approximately 60 percent of control group participants are expected to fall between Test 1 (baseline) and Test 4 (12 months after therapy) with falls reduced to around 40% in the two active therapy groups.

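### Fallers and multiple fallers, two of the three primary outcomes, are compared by relative risks with no stated allowance for unequal follow-up; the plan makes that allowance only for the falls rate

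*Protocol article*

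**What the plan says.** The Outcome measures section of the protocol article lists the primary outcomes as "i) the number of fallers in each group (ii) the number of multiple fallers in each group and (iii) the falls rate over 12 months". The Statistical analysis section then fixes a method for each:

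- Fallers and multiple fallers: "the number of fallers and multiple fallers in each group will be compared by calculating relative risks".
- Falls rate: "The number of falls and falls rate per person per year in the three groups will then be compared using negative binomial regression models". The reason given is that "This approach takes into account all falls and adjusts for varying duration of follow-up".
- Population: "All analyses will be conducted on an intention-to-treat principle using all randomised participants".
- The only method for first falls that handles censoring is confined to the treatment phase and labelled a safety measure: "time to first fall during the intervention period will be analysed using Kaplan-Meier survival analysis".

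The Sample size section states that "the drop-out rate was set at 15" per cent. It sizes the trial on the proportion of fallers, 60% in the control group against about 40% in each active group, at 110 per group.

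**The concern.** The authors expect follow-up to differ between people and treat this as a reason to choose the rate model. For the other two primary outcomes, one of which drives the sample size, they name a method with no term for observation time.

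A simple 12-month risk requires each randomised person to be a faller or a non-faller. Someone who stops the calendar at month 2 without a fall is neither. Counting that person as a non-faller keeps the full population but lowers the estimated risk, and lowers it more in the arm with more drop-out. Excluding that person departs from the stated population. The 15% allowance in the sample size protects precision; it does not settle how these people are classed.

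If drop-out differs between an exercise programme and a social programme, the faller ratio can shift in either direction with no change in the true effect.

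**Working it through.** **Inputs from the article.** Control risk 60%, active risk about 40%, so the planned ratio is 0.40/0.60 = 0.667. Power 80%, alpha 5% (taken as two-sided), drop-out 15%, 110 per group.

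**The plan's own figure.** With unpooled variance, n = (1.960 + 0.842)² × (0.6×0.4 + 0.4×0.6) / 0.2² = 94.2, so 95 per group. Then 95 × 1.15 = 109.3, rounded up to 110; dividing by 0.85 instead gives 112. The stated 110 reproduces, and the 15% is already inside it.

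**Assumptions not in the article.** (a) The hazard of a first fall is constant over the year. (b) Drop-out is spread evenly over the 12 months and is unrelated to falling. (c) People who leave without a recorded fall are counted as non-fallers. (d) Drop-out by arm is as shown below.

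**Formula.** With true 12-month risk p, the hazard is λ = −ln(1−p). A drop-out is seen to fall with mean probability m = 1 − p/λ. With drop-out proportion d, the observed risk is (1−d)p + dm.

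- Control: λ = 0.916, m = 1 − 0.6/0.916 = 0.345.
- Active: λ = 0.511, m = 1 − 0.4/0.511 = 0.217.

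**True ratio 0.667**

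| Drop-out, control / active | Observed control | Observed active | Ratio |
|---|---|---|---|
| 15% / 15% | 0.85×0.6 + 0.15×0.345 = 0.562 | 0.85×0.4 + 0.15×0.217 = 0.373 | 0.663 |
| 10% / 20% | 0.575 | 0.363 | 0.633 |
| 20% / 10% | 0.549 | 0.382 | 0.695 |

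Power at 110 per group (pooled normal approximation) is about 85% with complete follow-up, 81% at 15%/15% and 70% at 20%/10%.

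**No true effect (60% in both arms)**

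- 10% / 20%: 0.549/0.575 = 0.956. Rejection in the biased direction is 5.7% against a nominal 2.5%.
- 5% / 25%: 0.536/0.587 = 0.913.

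**If first falls cluster early.** Replace (a) by a gamma frailty with assumed variance 3. Then S(t) = (1 + 14.625t)^(−1/3), since 0.4^(−3) = 15.625. The mean of S over the year is 1.5 × (15.625^(2/3) − 1)/14.625 = 1.5 × 5.25/14.625 = 0.538, so m = 0.462. At 10%/20% with no effect, the observed risks are 0.586 and 0.572, and the ratio is 0.976.

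**Multiple fallers (two or more falls), assuming Poisson falls at the control hazard.** The 12-month risk is 1 − 0.4×(1 + 0.916) = 0.233. For drop-outs, m = 1 − 0.6/0.916 − 0.233/0.916 = 0.090. At 10%/20% with no effect: (0.8×0.233 + 0.2×0.090)/(0.9×0.233 + 0.1×0.090) = 0.205/0.219 = 0.935. A second fall needs more observed time, so the shift is larger.

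**If early leavers without a fall are excluded but early leavers with a fall are kept.** At 15% drop-out the control risk becomes 0.562/(1 − 0.15×(1 − 0.345)) = 0.562/0.902 = 0.623. The error now runs upward, and the population is no longer all randomised participants.

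**The case against.** The strongest reply has four parts.

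- **The classing rule is inferred.** The article says neither that the ratios are crude nor that early leavers count as non-fallers. A relative risk is an effect measure, and it could be formed from risks estimated with censoring or after imputation. A condensed article may leave that to a fuller document. This stands: a reader might infer that the plan does count early leavers as non-fallers, but the text does not say so. What remains is the contrast within one section, where adjustment for follow-up is attached to one method and not to the other.
- **At the plan's own figure the ratio hardly moves.** The single drop-out figure is 15%, with no difference between arms, and it gives 0.663 against 0.667. This also stands. The larger shifts need differential drop-out. The article gives no sign of it, and the three programmes are matched in length, group format and outpatient setting.
- **A constant hazard probably overstates the shift for first falls.** The choice of a negative binomial model implies that fall rates vary between people, which makes first falls cluster early. With the frailty assumed above, the null shift roughly halves, from 0.956 to 0.976. This stands, and the range should be reported. The same caution applies to the Poisson figure for multiple fallers.
- **The falls rate is also primary and is adjusted.** A follow-up artefact might show up as disagreement between the outcomes. This helps only in part, because a treatment can truly affect the proportion who fall and the number of falls differently.

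**Conclusion.** The point holds as a recommended change, not as a demonstrated bias. Two primary outcomes have a named method with no stated allowance for unequal follow-up, beside a third where the same section treats unequal follow-up as needing adjustment.

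Under equal, non-informative 15% drop-out, with early leavers counted as non-fallers, the harm is an understated absolute risk (control about 56% instead of 60%) and some loss of power. With an assumed 10-point difference in drop-out, a null ratio moves to between 0.956 and 0.976 when the active arm loses more. A true 0.667 moves to 0.633, or to 0.695 under the reverse pattern.

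Two stronger readings are tempting and are not supported. A reader might infer that the faller result will favour exercise; the direction depends on which arm loses more people, which the article does not predict. A reader might also infer that the secondary outcome "the number of injurious falls, defined as a fall requiring a visit to a health service provider" has no valid analysis, because a count without a baseline score fits neither rule for secondary outcomes. The negative binomial model already planned for all falls extends to a subset of them, and this is ordinary analysis detail.

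**What to change.** Keep the relative risk as the estimand and change how the risks are estimated. The Outcome measures section has participants mark the date of each fall, so the times exist. For each arm:

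- estimate the 12-month risk of a first fall (fallers) and of a second fall (multiple fallers, taken as two or more) by Kaplan-Meier, censoring at the last calendar entry;
- report the ratio of 12-month risks against control with confidence intervals;
- report the number who left early and the time observed, by arm.

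A complementary log-log model with log time as offset is not a substitute. It assumes a constant hazard and estimates a hazard ratio, which for 60% against 40% is ln(0.6)/ln(0.4) = 0.56, not the risk ratio of 0.67.

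The cost is analysis wording and some programming. Kaplan-Meier assumes non-informative censoring, as the planned rate model already does, and it gains nothing from people with no calendar data at all. A sensitivity analysis should therefore accompany it, letting the risk of falling after drop-out differ from that of people who stay, over a stated range and separately by arm.

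### The primary falls comparisons name follow-up time as their only adjustment, so prognostic baseline data the trial already collects go unused; the loss is in precision, not validity

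*Protocol article*

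**What the plan says.** The Outcome measures section of the protocol article gives three primary outcomes: "i) the number of fallers in each group (ii) the number of multiple fallers in each group and (iii) the falls rate over 12 months". The Statistical analysis section assigns the methods:

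- Fallers and multiple fallers: "the number of fallers and multiple fallers in each group will be compared by calculating relative risks".
- Falls rate: "The number of falls and falls rate per person per year in the three groups will then be compared using negative binomial regression models". The one stated adjustment follows: "This approach takes into account all falls and adjusts for varying duration of follow-up".
- Continuous secondary outcomes: "compared using analysis of covariance with baseline scores and intervention group entered as independent variables".
- Categorical secondary outcomes: "For categorical secondary outcome measures, relative risks will be used to analyse differences between the groups".

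Outcome measures also has every participant assessed before the 8-week programme. The measures listed there include walking speed, Timed Up and Go and the UPDRS: "Activity limitations will be quantified using the United Parkinson's Disease Rating Scale sections II and III". Under Participants, a Hoehn and Yahr rating above 4 excludes; the Discussion gives the enrolled range as 0 to IV.

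**The concern.** Fall counts in a population running from Hoehn and Yahr 0 to IV will differ widely between people. In a negative binomial comparison that between-person variation usually makes up most of the standard error of the log rate ratio. Baseline severity and mobility are plausible predictors of falling, and the Discussion itself plans to examine how impairment and disability relate to falls. The analysis paragraph spells out a baseline term for one class of outcome and names none for the primary outcomes, so the natural reading is a primary comparison by group with an exposure adjustment only.

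At stake is the width of the interval for the main result. There is also the risk that, if the arms differ by chance on severity, covariates are chosen after the data have been seen.

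**Working it through.** **1. Does the planned size rely on adjustment?** Inputs from Sample size: 60% versus 40% fallers, 80% power, alpha 5% (two-sided assumed), 15% drop-out.

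n per arm = (1.96 + 0.842)² × (0.24 + 0.24) / 0.20² = 94.2, so 95. Then 95 × 1.15 = 109.25, so 110; alternatively 94.2 / 0.85 = 110.8. The stated 110 is reproduced with no covariate.

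**2. Assumptions for the falls rate.** The article gives no mean rate, dispersion or covariate strength. Assume a control mean of 2.6 falls per person-year, between-person squared CV k = 2, and 110 × 0.85 = 93.5 evaluable per arm.

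Control fallers: 1 − (1 + 2 × 2.6)^(−1/2) = 60%, which matches the planned control proportion.

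**3. Unadjusted power for the rate.** Var(log RR) = [(1/μ₀ + k) + (1/μ₁ + k)] / n.

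- Rate ratio 0.6 (μ₁ = 1.56): (2.385 + 2.641) / 93.5 = 0.0538, SE 0.232. Power = Φ(0.511/0.232 − 1.96) = about 60%. This effect implies 1 − (1 + 2 × 1.56)^(−1/2) = 51% fallers in the treated arm, which is not the planned 40%.
- Planned 40% fallers with k = 2: μ₁ = (0.6⁻² − 1)/2 = 0.889, rate ratio 0.34. Var = (2.385 + 3.125) / 93.5 = 0.0589, SE 0.243. Power = Φ(1.073/0.243 − 1.96) = about 99%.

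**4. Effect of a baseline covariate at rate ratio 0.6.** Simulated trials with 94 per arm and total squared CV held at 2 were fitted by maximum-likelihood negative binomial with and without the covariate. Variance reductions come from three separate runs, power from two of them (400 and 800 trials per setting).

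| Covariate rate ratio per SD | Cut in variance of log RR | Power, unadjusted to adjusted |
|---|---|---|
| 1.35 | 7%, 9%, 12% | 58% to 59%; 65% to 66% |
| 1.65 | 20%, 21%, 23% | 64% to 69%; 68% to 74% |
| 2.0 | 36%, 37%, 38% | 70% to 82%; 68% to 80% |

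Hand check on direction: with a normal covariate of log rate ratio b per SD, the residual squared CV is 3/exp(b²) − 1, which is 1.74, 1.33 and 0.86 for the three rows. Putting these for k in the formula of step 3 gives variance ratios of 4.51/5.03, 3.69/5.03 and 2.74/5.03, or cuts of about 10%, 26% and 46%. This shortcut places everyone at the arm mean and so overstates the gain; the simulated figures are the ones to use.

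In these simulations 61% to 68% of controls fell. The strongest setting, at about 68%, fits the planned 60% least well.

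**5. Other assumed rates.** Set k so that 60% of controls fall, take a rate ratio of 0.7, and replace k by k(1 − R²), where R² is the share of between-person variation explained.

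| Control mean per year | k | R² | Cut in variance |
|---|---|---|---|
| 1.5 | 1.0 | 0.1 | 5.5% |
| 3 | 2.2 | 0.2 | 17% |
| 3 | 2.2 | 0.3 | 25% |
| 10 | 4.1 | 0.5 | 49% |

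At a mean of 3 per year, power goes from 32% unadjusted to 38% (R² 0.2) or 41% (R² 0.3).

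**6. Faller proportion.** Approximating on the risk-difference scale, power = Φ(0.20 / √[0.48(1 − R²)/93.5] − 1.96). R² of 0, 0.05 and 0.20 gives 80%, 82% and 88%.

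**The case against.** The strongest reply is that the article is silent on covariates rather than ruling them out. It condenses a fuller protocol, a covariate list often sits in the analysis plan, and neither is shown. That stands to this extent: a reader might infer that the sponsor has declared the primary models unadjusted, and the text does not say so. What remains is that the paragraph is not silent in general. It states an adjustment for follow-up in the falls model and baseline terms elsewhere, so group plus exposure is the fair reading of what is written.

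A reader might also infer an inconsistency between primary and secondary outcomes. The documents do not support it. Only continuous secondary outcomes are adjusted, each for its own baseline score; categorical secondary outcomes get relative risks with no baseline term named, just like fallers. The split follows outcome type, and no baseline falls count is described that could serve the rate in the same way.

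Nor is the primary result biased or the trial undersized for want of covariates: an unadjusted comparison of randomised arms is valid, and step 1 shows that the sample size does not need adjustment. Finally, it would be wrong to conclude that falls history is not collected, since the article refers to baseline data without listing every item.

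The objection that the gain depends on chosen inputs is also correct. With a weak covariate the power gain is about one point.

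**Conclusion.** The point holds as an inexpensive improvement in efficiency, not as an error. As written, the primary falls outcomes are compared by group with adjustment only for follow-up duration, while baseline severity and mobility measures are available and unused in that comparison. Under the assumptions of step 2 and a covariate rate ratio of 1.35 to 2.0 per SD, the variance of the log rate ratio falls by roughly 7% to 38%, and power at an assumed rate ratio of 0.6 rises by about 1 to 12 points. Under the planned 60% versus 40% fallers with the same dispersion, power for the rate is already about 99% and the benefit is a narrower interval only. Mean rate, dispersion, covariate strength and the 0.6 rate ratio are all assumptions. The direction of the effect on variance is the same across every value tried; its size cannot be fixed from the article.

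**What to change.** In the Statistical analysis section, prespecify two baseline covariates for the negative binomial model: UPDRS motor score (or Hoehn and Yahr stage) and Timed Up and Go, keeping follow-up time as exposure. For fallers and multiple fallers, report relative risks adjusted for the same covariates, for example by modified Poisson or log-binomial regression, so that the effect measure stays a relative risk. Keep the unadjusted results as a sensitivity analysis. If falls history is already recorded at baseline, add it to the list. If a fuller plan already names covariates, it is enough to say so here.

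The cost is a few sentences, plus regression models in place of directly calculated relative risks for two outcomes. It needs no extra visits, no new measurements and no change in sample size.
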